## Abstract

**Background:**

During the hospitalization period, it is possible to observe considerable changes in the vital parameters of patients, which may require emergency interventions or intensive treatment. The alteration of signs and symptoms that lead to physiological instability that can worsen the clinical picture with progression to shock, respiratory failure, or cardiorespiratory arrest is currently defined as clinical deterioration. Identifying signs of clinical deterioration at an early stage can lead to substantial decreases in mortality rates, the need for emergency interventions, and unscheduled treatments in intensive care units. Identifying and appropriately referring patients who show signs of clinical deterioration can be facilitated by applying early warning systems that provide rapid responses. The nursing team is usually the first to identify clinical changes in patients. Although the literature demonstrates that early recognition of clinical deterioration is the key to early intervention and leads to better outcomes, we only sometimes pursue the most appropriate intervention.

**Objective:**

This study aims to implement and evaluate an evidence-based professional training program designed for nurses and coordinated by a nurse using the “just-in-time” methodology and the National Early Warning Score 2 (NEWS2) to assess the risk of early clinical deterioration and appropriate referral in inpatient units of a public university hospital in southeastern Brazil.

**Methods:**

This intervention protocol is structured according to the recommendations of the SPIRIT (Standard Protocol Items: Recommendations for Interventional Trials) Declaration 2013. The type of training to be offered, “Just-in-Time Training,” consists of a teaching modality that facilitates the delivery of a time-based and work-based education, with greater emphasis on providing on-the-job learning as needed. A qualitative stage will also be conducted through focus groups and interviews with nurses to verify the factors that influence the professional practice related to the early evaluation of the clinic. A script of previously tested questions will guide and standardize the different groups. The data will define the intervention’s elements: the strategy, the type of training, the location, the teaching methodology, and the teaching material.

**Results:**

The study has received authorization from the ethics committee, and participants will be recruited in July 2023. Data collection should be completed in October of the same year. The results obtained at the end of this research will be shared with the participating nursing team through the presentation of reports. In addition, the research results will be submitted to scientific journals and presented at international scientific conferences.

**Conclusions:**

This study will support nurses and possibly other clinicians to improve their approach to early recognition of clinical deterioration in patients.

**Trial Registration:**

Brazilian Registry of Clinical Trials RBR-5hq9y3k; https://ensaiosclinicos.gov.br/rg/RBR-5hq9y3k

**International Registered Report Identifier (IRRID):**

PRR1-10.2196/47293

## Introduction

A patient’s clinical deterioration originates from physiological changes detected by monitoring vital signs, which can indicate early or potentially critical patients who need special monitoring in the wards [1,2]. Such changes can indicate a greater probability of cardiorespiratory arrest and lead to unplanned hospitalizations in intensive care units and death [3]. If there is a delay in the identification of these patients, it will result in delayed intervention and, therefore, in the increase of hospital mortality. The early identification of alterations in vital signs can facilitate greater efficiency in the care provided to the patient because the reduction in morbidity leads to a reduction in the length of hospital stays and lower expenditure on health, which can guarantee a better quality of care [1,4].

The nursing team is usually the first to identify clinical changes in patients. The nursing team comprises a diverse group of health care professionals collaborating to deliver patient care. This team typically includes registered nurses, licensed practical nurses or licensed vocational nurses, certified nursing assistants, nurse practitioners, nurse managers or supervisors, clinical nurse specialists, and additional support staff. These professionals possess specialized skills and training, allowing them to provide comprehensive care, administer treatments, monitor patient conditions, and fulfill administrative responsibilities. The composition of the nursing team may vary based on health care settings and specific patient needs.

The evaluation of vital signs is a routine activity of the nursing team in the hospital and is of extreme importance as it tracks the evolution of the clinical picture and the individual’s health and can predict clinical deterioration. Intrinsically, nursing is linked to patient surveillance and monitoring changes that may indicate warning signs, and these factors are interlinked with survival outcomes in cases of in-hospital cardiorespiratory arrest. Therefore, the nursing team can predict these events early to increase patient safety and prevent this clinical deterioration [5].

Early recognition of clinical deterioration is the key to early intervention and can lead to better patient outcomes [5]. Early warning systems are designed to detect changes and activate rapid response teams to minimize complications resulting from the degradation of the patient’s clinical condition before reaching a critical state of complex regression, which can be fatal [6]. Various systems have been described in the literature that use simple physiological parameters and routine assessments performed daily by nurses to manage the risk of degradation of the patient’s clinical status by adapting the level of care they need [7]. These systems are used to identify and respond efficiently to the needs of patients in an acute situation or phase [8].

Considering the PICOT (Population, Intervention, Comparison, Outcome, and Time) approach [9], this training was designed with nurses working in a hospital setting as the population of interest, the implementation of a professional training program for early clinical deterioration risk assessment as the intervention, the standard practice without the professional training program (ie, pretraining and posttraining) as the comparison, the improved identification and appropriate referral of patients showing signs of clinical deterioration as the outcome, and before and after the implementation of the professional training program as the timeframe. Therefore, the following research question guided the development of this training: “In nurses working in a hospital setting, does the implementation of a professional training program for early clinical deterioration risk assessment (compared to standard practice without the program) improve the identification and appropriate referral of patients showing signs of clinical deterioration?”

Considering this research question and given the options available in the literature of instruments that aim to facilitate the assessment of clinical deterioration, we decided to develop a training project for nurses to assess early clinical deterioration in a university hospital through the use of an alert scale designed for early identification of signs of clinical deterioration in patients. This protocol aims to implement and evaluate an evidence-based professional training program designed for nurses and coordinated by a nurse using the “just-in-time” methodology and the National Early Warning Score 2 (NEWS2) to assess the risk of early clinical deterioration and appropriate referral in inpatient units of a public university hospital in southeastern Brazil.

## Methods

This study was structured according to the recommendations of the SPIRIT (Standard Protocol Items: Recommendations for Interventional Trials) Declaration 2013 (Multimedia Appendix 1) [10].

### Trial Design and Settings

A quasi-experimental study of the type before and after, with a single arm, will be conducted with all nurses from inpatient units of a tertiary-level university hospital in the interior of the southeast of São Paulo to implement a training program to assess the risk of early clinical deterioration. This study aims to demonstrate causality between the proposed intervention and the nurses’ ability to use the NEWS2 tool to assess the patient’s clinical deterioration and provide appropriate referrals. Quasi-experimental designs are often used when assigning participants randomly to different groups is not feasible or ethical. This allows for intragroup comparison of outcomes (ie, comparing the pretraining and posttraining results in the same group). In this study, having only a subset of the staff receiving the training would not be feasible. Although a quasi-experimental design does not offer the same level of control as a randomized controlled trial, it can provide valuable insights into the effects of the training program because it offers a real-world evaluation of the intervention’s impact within the specific setting and considers the practical constraints of implementation.

The trial was registered in the Brazilian Registry of Clinical Trials (ReBEC) with the number RBR-5hq9y3k. For the design of the method, the limits of the Guideline for Reporting Evidence-Based Practice Educational Interventions and Teaching (GREET) [11] were respected.

### Eligibility Criteria

All assisting nurses allocated to the university hospital’s clinical and surgical hospitalization units in the interior of São Paulo will be included. During the data collection period, nurses who are inactive or on health or maternity leave or vacation will be excluded because they cannot be invited to participate in the training due to labor legislation issues.

### Intervention

The type of training to be offered, known as “Just-in-Time Training” (JITT), consists of an education modality that facilitates the delivery of time-relevant and work-based education, with a greater emphasis on teaching provision at work as needed [12]. JITT is a training approach that focuses on providing relevant and specific information to individuals when they need it to perform a task or solve a problem and is designed to provide immediate and targeted support, allowing nurses to acquire knowledge or skills quickly and efficiently. JITT is often used in contexts where time is limited and there is a need for spontaneous and on-demand learning. The effectiveness of the JITT method stems from several factors, such as punctuality, contextualization, and flexibility. By providing nurses with the correct information at a convenient time and place, JITT increases learning efficiency, minimizes continuums, and empowers individuals to quickly acquire the knowledge and skills they need to perform effectively in their specific tasks or problem-solving scenarios [12].

The JITT approach to recognizing and responding to patient deterioration has theoretical and educational relevance in its design. Education takes place in the clinical setting using real meetings with patients to guide the content. This approach is closely aligned with learning through a theory of practice, as the literature recommends [13]. In this perspective, workplaces are viewed as learning environments; optimizing the experiences provided by health workplaces, increasing learning potential, and promoting the involvement of workers can improve workers’ ability to respond to future occupational challenges.

The training program developed for nurses was based on the intervention mapping [14] protocol that describes the path from problem identification to problem solution or mitigation. Each of the six stages of intervention mapping comprises several tasks, integrating theory and evidence. Completing tasks in one step creates a product that drives the subsequent step. Completing all steps serves as a model for designing, implementing, and evaluating an intervention based on theoretical, empirical, and practical information.

#### Needs Assessment: A Theoretical and Experiential Approach

The needs assessment will be gathered by reviewing the literature on nurses’ knowledge and use of early deterioration tools. To use the experiential approach, a qualitative step will be conducted through the realization of focus groups and interviews with nurses from inpatient units to verify the factors that influence professional practice related to the early assessment of clinical deterioration. A script of previously established questions will guide and standardize the different groups (Textbox 1). The invitation to nurses will be made through a direct approach by verbal invitation from the researcher herself.

The interviews and focus groups will be based on a pre-established script (Textbox 2). All groups will have their audio recorded for future analysis, with the saturation criterion as a parameter for the decision to stop collection. The data collected in this phase will be evaluated through content analysis.

Presentation of the project in the focus groups.Team presentation: 3 nurses.Aims: Invite nurses to participate in a project offering training on early assessment of clinical deterioration.Planning: After agreeing and signing the consent form, the nurses will participate in a 30-minute focus group meeting. Six months after the meeting, training will be offered. Those who participate will receive feedback and a certificate.Setting: Nursing Department, University Hospital.

Script to guide focus groups.Do you know what early assessment of clinical deterioration in patients is?Do you usually perform an early assessment of the clinical deterioration of patients admitted to the wards? If so, how?For you, what is the importance of this assessment in your daily work in the ward?Do you use data from early clinical deterioration assessment to guide the care plan of patients under your supervision? If so, what data? How?Do you think it is feasible to carry out an early assessment of the clinical deterioration of patients admitted to the wards?In your opinion, what factors can favor the early assessment of clinical deterioration of patients admitted to the wards?In your opinion, what factors can hinder the early assessment of clinical deterioration of patients admitted to the wards?How would you like to receive this training? Reflect and give your opinion on the best strategy, the type of training, location, teaching methodology to be used and teaching material.

#### Establishment of Training Objectives

Following the needs assessment stage, we will establish the training objective. The most appropriate content and training strategies for the target population and context should be identified at this stage. The data obtained will allow us to define the elements of the intervention, including the strategy, type of training, location, teaching methodology, and teaching material.

#### Intervention Strategy Proposal

In this stage, the content to be addressed, the methods design, and the strategies and means of communication will be defined.

#### Pretest

This phase will consist of a pretest of the intervention applied to a population subsample to verify operational aspects of the chosen content, strategy, and means of communication. This step aims to assess the adequacy and feasibility of the proposed intervention.

#### Preintervention Assessment

In this step, a questionnaire [15] will be used to assess the theoretical content related to each participating nurse’s early assessment of clinical deterioration to compare the pretraining and posttraining results. The Brazilian version of the rapid response team (RRT) survey, which aims to explore nurses’ knowledge and perceptions of RRTs, was translated and adapted into Brazilian Portuguese and validated ([name] and [name], unpublished data). This instrument has 3 parts: part 1 contains 4 hypothetical case studies; in part 2, respondents must evaluate each factor according to its degree of importance; and in part 3, participants must include their basic information regarding characteristics and work history.

Although this tool has been widely used globally, no studies have been published on its psychometric properties. Assessing the psychometric properties of a measurement tool is relevant for ensuring its validity, reliability, and suitability for data collection in most research contexts. However, there are situations where a psychometric evaluation may be unnecessary, such as for well-established and widely used tools, especially those that do not measure psychosocial constructs (eg, the RRT survey). Once the tool has been extensively used, widely accepted, and has a solid empirical foundation in the literature, conducting a full psychometric assessment may not be necessary [16].

#### Implementation of the Intervention

The planned intervention will be implemented via the chosen method, and the participants will be informed in advance to allow for planning and effective participation.

#### Postintervention Assessment

In this step, the Brazilian version of the RRT survey will be reapplied to compare the pretraining and posttraining results and evaluate the effectiveness of the intervention.

#### Assessment of Suitability, Acceptability, and Quality of the Intervention

The nurses’ assessment regarding the suitability, acceptability, and quality of the proposed intervention will be assessed through a self-answered, open-questions questionnaire. This questionnaire will have its content submitted for validation by specialists.

#### Criteria for Discontinuing or Modifying Allocated Interventions for a Given Trial Participant

Participants will be discontinued for not attending scheduled meetings or ending participation in the study during the intervention or data collection phase.

#### Strategies to Improve Adherence to Intervention Protocols and Procedures for Monitoring Adherence

An SMS text message will be sent to participants’ telephones a day before the scheduled appointment, reminding them to attend the training.

#### Relevant Interventions That Are Permitted or Prohibited During the Trial

During the intervention, participants must not engage in any other training regarding clinical deterioration.

### Outcomes

A form for analyzing the sociodemographic profile will be applied to nurses with the following variables: age, sex, education level, time of training, place, and time of work in the unit.

The effect of evaluating the theoretical content related to the early assessment of clinical deterioration by each participating nurse will be considered to compare the pretraining and posttraining results.

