### Auditing

The following audit procedures will be considered: (1) compliance audits, by assessing the extent to which nurses are complying with the prescribed training protocol (ie, reviewing records, documentation, and training logs to verify if nurses have completed the required modules, attended relevant sessions, or fulfilled certification requirements); (2) knowledge assessments, by assessing nurses’ understanding of the content; (3) skills evaluations, by observing and assessing nurses’ performance of the specific skills or procedures required through direct observation, simulated scenarios, and practical assessments; (4) feedback surveys, to gather feedback from nurses about their training experience; and (5) quality assurance reviews of training materials, resources, and procedures, to ensure they align with evidence-based practices.

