### Conclusions

This study aims to contribute to advancing nursing practices in the context of clinical deterioration among inpatients. The intervention proposed in this research is grounded in established theoretical principles and is characterized by its cost-effectiveness and ease of implementation. Specifically tailored for adult patients in inpatient units, this program holds the potential to substantially enhance nurses’ ability to accurately diagnose and promptly intervene in cases of early clinical deterioration. The paper introduces an evidence-based professional training program designed for nurses and led by a nurse, implementing a risk assessment protocol for early clinical deterioration within the inpatient units.

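### The question and aim are about recognising and referring deteriorating patients, but the planned measures are survey and NEWS2 scores taken around one training session, which cannot show a change in ward practice

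*Protocol article*

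**What the plan says.** The Introduction sets out the PICOT elements and names "the improved identification and appropriate referral of patients showing signs of clinical deterioration as the outcome". The research question follows in the same terms. Trial Design and Settings moves the aim to nurse level: the study is meant to show a causal link between the training and "the nurses’ ability to use the NEWS2 tool to assess the patient’s clinical deterioration and provide appropriate referrals".

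The Outcomes section lists a sociodemographic form and then one effect measure: "The effect of evaluating the theoretical content related to the early assessment of clinical deterioration by each participating nurse will be considered", compared before and after training. The instrument is the Brazilian RRT survey, "which aims to explore nurses’ knowledge and perceptions of RRTs". Preintervention Assessment says that "part 1 contains 4 hypothetical case studies". Postintervention Assessment reapplies the survey to judge effectiveness.

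A second before-after measure appears elsewhere. Sample Size and Sampling asks for at least 50 nurses to assess how NEWS2 is filled out before and after training. Statistical Analysis compares the NEWS2 score and the RRT part 1 score between the two times by paired t or Wilcoxon tests.

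Data Collection gives each nurse a single 1-hour session in a hospital training room, holding the presentation, consent, pretest, training, posttest and final evaluation. It then states that any rise in the RRT survey or web-based questionnaire score counts as improvement and so as effectiveness.

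**The concern.** The document fixes one outcome in its research question and a different one in its Outcomes section. This is a conflict between stated passages, not detail left to a fuller document. It matters because of the decision rule. A higher score shortly after teaching would, under the plan, be reported as effectiveness, and the question it would be read against is whether patients are better recognised and referred. Hospital managers, whom the dissemination plan names as an audience, could take a test result as evidence about ward practice.

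The Limitations section does not guard against this. It covers generalisability, selection, the length of the data collection period, self-report in the qualitative stage and uncontrolled confounding. It does not say that patient recognition and referral go unmeasured. It even lists patient demographics as a confounder, a worry that fits a patient-level outcome better than a nurse's test score.

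**Working it through.** **Step 1: the plan's own figure.** Inputs from Sample Size and Sampling: paired t test, significance level 5%, power 80%, effect size d = 0.50, stated minimum 34, planned 50. Sidedness is not stated; two-sided is assumed. Power is P(|T| > t(0.975, n−1)), where T is noncentral t with n−1 degrees of freedom and noncentrality d·√n.

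- n = 33: noncentrality 0.50 × √33 = 2.87, power 0.795.
- n = 34: noncentrality 0.50 × √34 = 2.92, power 0.808. The stated minimum of 34 is reproduced.
- n = 50: noncentrality 0.50 × √50 = 3.54, power 0.934. The smallest effect detectable with 80% power is d = 0.404.

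These figures apply to the RRT part 1 score. The document gives no rate, standard deviation or effect size for recognising or referring patients, so no sample size can be computed for that outcome.

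**Step 2: question against measures.**

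| Place | What it concerns | Recognition or referral of real patients measured? |
|---|---|---|
| Introduction (PICOT, research question) | Patients recognised and properly referred | This is the target |
| Trial Design and Settings | Nurses' use of NEWS2 and their referrals | This is the target, at nurse level |
| Outcomes | Theoretical content, before and after | No |
| Pre- and Postintervention Assessment | RRT survey; part 1 is hypothetical cases | No |
| Sample Size; Statistical Analysis | NEWS2 completion score | No; bears on NEWS2 use only |
| Auditing | Skills evaluation "through direct observation, simulated scenarios, and practical assessments" | Not an outcome; audit procedures are only to be considered |

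**Step 3: timing.** Pretest and posttest are steps of one 1-hour session, and each nurse attends once. No shift falls between them. A change in how nurses recognise or refer patients on the ward therefore cannot appear in the before-after difference, whatever its size and however many nurses take part.

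**Step 4: the inference.** The plan's rule runs from a score rise to effectiveness. Steps 2 and 3 show that the score rise can support a statement about immediate test performance and, through the NEWS2 score, about completing the tool. It cannot support a statement about referral in practice.

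**The case against.** The best defence is that the measures come closer to the aim than the Outcomes section suggests. Much of that stands.

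- A reader might infer that survey knowledge is the only planned outcome. It is not. The NEWS2 score has its own sample-size justification and its own paired test, and it bears directly on the NEWS2 half of the aim in Trial Design and Settings. What remains is that the Outcomes section omits it and the article does not describe how it is scored.
- A reader might infer that the survey tests only theory. The items are not shown. Four hypothetical cases in a survey about rapid response teams may well touch on recognition and escalation decisions. They are still not patients, and the article does not say that they are scored that way.
- A reader might infer from the Auditing section that observed-skill data will be collected and left unanalysed. That section says only that such audits will be considered. It does not commit to assessing every nurse, scoring before training, or rating referral decisions.

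It may also be said that a nurse-level aim makes patient-level data unnecessary. That answers the PICOT wording only in part, because the nurse-level aim itself includes making appropriate referrals, and no planned measure is described as capturing that.

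The claim in Conclusions that the intervention "is characterized by its cost-effectiveness and ease of implementation" has no cost variable behind it anywhere in the document. It is a side issue: it is neither an objective nor an analysis, and it does not affect whether the outcome fits the question.

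**Conclusion.** The point holds in this form. The research question and aim concern recognition and referral of deteriorating patients. The Outcomes section lists theoretical knowledge, and NEWS2 completion is planned only in the sample-size and analysis sections. Neither measures recognition or referral of real patients. With both measurements in one session, a change in ward practice cannot appear, yet a score rise is to be read as effectiveness. Neither of the two parts of the question is measured in patients. The data remain usable for a narrower conclusion, and the sample size is not at fault.

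Two assumptions matter. First, NEWS2 completion is taken to belong to the pretest and posttest in that session, because the article places it nowhere else. If it were taken on the wards, it would say something about use of the tool in practice but still nothing about referral. Second, RRT part 1 is taken as described, since its items cannot be inspected. If its cases do ask for escalation choices, it would measure hypothetical decisions, not referrals made.

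**What to change.** 1. In the Introduction, in Trial Design and Settings and in the matching objective statements, restate the question and aim along these lines: *the immediate change, from before to after a single training session, in nurses' RRT survey part 1 score (knowledge and responses to hypothetical cases) and in their accuracy in completing NEWS2.*
2. In Outcomes, list the NEWS2 score beside the RRT part 1 score, so that this section matches Sample Size and Statistical Analysis.
3. In Data Collection, limit the effectiveness statement to these measures.
4. In Limitations, state that recognition and referral of patients on the wards are not measured.
5. As a minor point, remove the cost-effectiveness statement from Conclusions.

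All five are wording changes. They need no extra data, session time or nurses, and the planned 50 stands.

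Making simulated scenarios a scored outcome is not recommended as the remedy. Individual scoring before and after training would not fit the already full hour, would probably need assessors, and would still not measure referral on the ward.
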